| Study design:                   | 
This is a pragmatic multicentre, 2x2 factorial randomized controlled trial with 1:1:1:1 randomization to switching to DTG-based maintenance dual therapy in association with FTC or continuation of cART, and to patient-centered monitoring or continuation of standard monitoring.
 
The randomized comparisons will examine whether DTG + FTC dual therapy is non-inferior in terms of viral suppression compared to standard therapy, and whether patient-centered monitoring is cost-saving and acceptable compared to standard monitoring.
 
Patients will be followed during 48 weeks.
 
A sample size of 92 patients in each group (DTG + FTC dual therapy and standard cART) will be required to demonstrate non-inferiority with a non-inferiority (NI) margin of 12%.
                                                                                                                                                                                                                                                                                                                                                                                                                                                                                                                             |

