### 5.2 Secondary Outcomes

1. Proportion of patients maintaining HIV suppression defined as HIV-RNA <50 copies/ml throughout 48 weeks (+/- 21 days). A single blip defined as HIV-RNA <200 copies/ml during the study period is allowed as long as this value is followed by HIV-RNA <50 copies/ml;
2. Proportion of patients with HIV-RNA < 50 cp/ml at week 48 by FDA snapshot analysis; Proportion of patients experiencing loss of future drug options defined as new intermediate or high-level resistance to one or more drugs to which the patient's virus was considered sensitive at trial entry;
3. Time to loss of virological response (TLOVR) up to week 48 defined as the first of the two-confirmed HIV-RNA >100 copies/ml (at least two weeks apart);
4. Change in CD4 cell count from baseline to week 48 +/- 21 days;
5. Change in HIV-DNA level from baseline to week 48 +/- 21 days;
6. Change in lipidic profile (total cholesterol, high density lipoprotein-cholesterol, triglycerides, and low density lipoprotein-cholesterol) from baseline to week 48 +/- 21 days;
7. Change in glucose profile from baseline to week 48;
8. Change in Framingham-calculated cardiovascular risk from baseline to week 48;
9. Change in glomerular function rate from baseline to week 48;
10. Proportion of patients with an adverse event throughout week 48;
11. Proportion of patients with a serious adverse event (SAE) throughout week 48;
12. Proportion of patients with a CNS adverse event throughout week 48;
13. Proportion of patients new to DTG with CNS symptoms at 2 and 6 weeks after starting DTG;
14. Change in patients' health-related quality of life from baseline to weeks 12 and 48;
15. Assessment of patient's monitoring satisfaction from baseline to weeks 24 and 48 for patients in the patient-centered monitoring arm;
16. Assessment of the global satisfaction of the monitoring at week 48 for all patients (regardless of the randomisation arm);
17. Proportion of patients in the patient-centered monitoring arm expressing willingness to change monitoring options throughout 48 weeks;
18. Assessment of patient's treatment satisfaction at week 48;
19. Assessment of ARV treatment in the post study;
20. Study satisfaction at week 48;
21. Cost-effectiveness of study arms at 48 weeks;
22. Changes in patient weight from baseline to week 48.

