## **6.2 Methods of minimising bias**

### **6.2.1 Randomisation**

#### Allocation sequence

Patients will be randomised 1:1:1:1 using randomly-permuted blocks of varying sizes to one of the four study arms (one computer-based randomization list stratified per study center).

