### 11.2 Determination of Sample Size

The first sample size calculation was based on the primary outcome for the comparison between DTG + FTC dual therapy and standard cART, i.e. the comparison between the proportions of patients in the two arms maintaining virologic suppression, using a two-sample proportion test (96). The following assumptions were made:

- Power 80%
- Significance level 0.025 (one-sided Z test of non-inferiority)
- 97% of patients with conventional cART will be virologically suppressed at week 48 (<100 copies/ml)
- 94% of patients on DTG + FTC dual therapy will be virologically suppressed at week 48 (<100 copies/ml)
- Non-inferiority margin of 12% (as in previous non-inferiority trials)(97-104). We chose 12% noninferiority margin because there is no difference in terms of resistance acquisition between 10% and 22% virological failure.

Sample size of 83 patients in each group (total sample size, 166 patients) to achieve 80% power to detect a non-inferiority margin difference between the group proportions of -0.12 was calculated. The power was computed for the case when the actual cART group proportion is 97% and the actual DTG + FTC dual therapy group proportion is 94%. To allow for at least 10% loss to follow-up and also for the randomisation in two steps in this 1:1:1:1 trial, we will aim to recruit **a total of 184 patients**.

The second sample size calculation was based on the primary outcome for the comparison between simplified monitoring and standard monitoring, i.e. the comparison between mean direct costs in the two arms (105). The following assumptions were made:

- Significance level 0.05 (two-sided t-test)
- Direct costs are CHF 25,000 per year (standard deviation (SD) CHF 8,000) with conventional monitoring
- SDs are equal in the two groups (CHF 8,000)

With sample sizes of 92 patients in each group, we will have approximately 55% power to detect a 10% difference in costs, and 99% power to detect a 25% difference in costs. We will also have substantial power to detect small-to-moderate differences in many of the secondary outcomes, e.g. changes in CD4 cell counts or health-related quality of life. The exceptions are rare outcomes such as adverse events, resistance or clinical complications for which the statistical power to detect differences will be low.

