#### 11.4.2 Primary analysis

As a first step in this factorial trial, we will test for an interaction between the type of drug treatment and the monitoring type in order to assess if treatment effect is different depending on the type of monitoring. If the test is non-significant we will combine the two types of monitoring for the drug therapy comparison and the two drug therapies for the monitoring comparison. Otherwise, the trial will be analysed as a four-arm trial with a hierarchical testing approach.

For the primary comparison of the primary outcome between the two treatment arms, we will obtain the proportion of patients with viral suppression for 48 weeks in each arm, and compute a Mantel-Haenszel risk difference (DTG+FTC - cART) stratified for the monitoring type with a two-sided 95% confidence interval (107). If the lower confidence limit is higher than -12% we will conclude non-inferiority. If the lower confidence limit is below -12% we will conclude that DTG + FTC is potentially inferior to cART.

For the secondary comparison of the primary outcome between the two monitoring arms, we will calculate a Mantel-Haenszel test statistics and Mantel-Haenszel risk difference (DTG+FTC - cART) stratified for the type of treatment.

Secondary categorical outcomes (proportions of virological suppression <50 copies/mL both as a standard proportion and as FDA snapshot, of loss of future treatment options, of adverse events, of serious adverse events, of CSN adverse events, of CNS symptoms) between the DTG+FTC and cART groups, and between the patient-centered and standard monitoring groups will also be analysed using the Mantel-Haenszel test statistics and Mantel-Haenszel risk difference (DTG+FTC - cART) stratified for the type of monitoring and type of treatment, respectively.

For continuous outcome variables (CD4 count, HIV-DNA level, total cholesterol, high-density lipoproteine, triglycérides, low density lipoprotein-cholesterol, glucose, Framingham-calculated cardiovascular risk, glomerular function rate, weight, health-related quality of life, treatment satisfaction), we will compare the mean values at 48 months between the DTG+FTC and cART treatment groups and between the patient-centered and standard monitoring groups using linear regression adjusted for the type of monitoring and type of treatment, respectively.

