Time to loss of virological response (TLOVR) will be graphically depicted by Kaplan-Meier curves, and evaluated by a univariable and multivariate Cox proportional Hazard model, adjusted for stratified for the type of monitoring and type of treatment.

Predictors of virological failure (nadir CD4 count, baseline HIV-DNA, zenith HIV-RNA, years since HIV infection, years of viral suppression, CD4/CD8 ratio, age, DTG and FTC plasma concentrations, pharmacogenetic analysis, any other relevant clinical or laboratory parameters) will be assessed using forward stepwise multiple logistic regression.

Economic analyses will be performed from the health provider perspective. A multiple linear regression model will be performed to compare the mean direct costs between the two monitoring strategies after adjustment for the treatment arm.

All analyses will be performed in the PP dataset and in the ITT dataset.

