### **11.5 Handling of missing data and drop-outs**

The following strategies will be used to replace missing values at the final study timepoint. If HIV-RNA is available at week 36, the value at time 36 will be considered (last observation carried forward). If no data is available at weeks 36 and 48, we will consider these patients as failures. The same approach will be considered for secondary outcomes. For continuous outcomes, we will exclude patients from the analysis if no data is available at weeks 36 and 48. In the snapshot analysis, patients with missing outcome in the time snapshot window will be considered as failures. Sensitivity analyses will be performed to determine whether the conclusions are sensitive to assumptions about the missing-data mechanism. We will compare patient characteristics between the two groups having or not missing data in order to assess their similarity. If differences are outlined, missing data would be considered not at random and some bias in the estimation of treatment effect would be suspected. If not, we will consider the complete case analysis as valid to estimate the noninferiority of DTG+FTC compared to standard treatment.

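### The main analysis of continuous outcomes omits the baseline value and names a non-existent month-48 time point; for routine laboratory outcomes, week-36 carry-forward can work in only one monitoring arm

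*Protocol*

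**What the plan says.** **Outcome definitions.** Section 5.2 lists CD4 count, HIV-DNA, lipids, glucose, Framingham risk, glomerular function, quality of life and weight as changes from baseline. For CD4 the wording is "Change in CD4 cell count from baseline to week 48 +/- 21 days". Section 5.4 repeats most of them as safety outcomes.

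**Main analysis.** Section 11.4.2 says "we will compare the mean values at 48 months between the DTG+FTC and cART treatment groups", with a parallel comparison of the monitoring groups, "using linear regression adjusted for the type of monitoring and type of treatment, respectively". There is no change score and no baseline term.

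**Duration.** The synopsis says "Patients will be followed during 48 weeks". Section 13 adds post-study visits at weeks 96 and 144, analysed by the methods of section 11.

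**Missing data.** Section 11.5 carries the week-36 HIV-RNA value forward when week 48 is missing and says that the same approach will be considered for secondary outcomes. It then adds: "For continuous outcomes, we will exclude patients from the analysis if no data is available at weeks 36 and 48".

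**Week-36 measurements.** Table 1 in section 8.1.1 gives the patient-centered arm HIV-RNA only at week 36. Section 9.3.5 restricts CD4 count, blood count and safety chemistry with lipids to the standard-monitoring arm. The exception is glucose and creatinine in patient-centered patients who take DTG with metformin.

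**Centre.** Section 6.2.1 describes "one computer-based randomization list stratified per study center". No model in section 11.4 names centre. The cost regression is to be used "to compare the mean direct costs between the two monitoring strategies after adjustment for the treatment arm".

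**The concern.** Three parts of the plan do not fit together.

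1. The outcomes are changes, but the main model looks only at the follow-up value. In patients stable on suppressive therapy, the baseline value is likely to be the strongest single predictor of the week-48 value. Leaving it out adds noise and lets a chance baseline difference pass into the estimate. The time point is also wrong as written, and section 13 passes the same model on to weeks 96 and 144.

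2. The carry-forward rule relies on a visit at which, by design, one monitoring arm does not have these measurements. Section 4.4 names CD4 count, cholesterol, Framingham risk and glomerular function as safety parameters for simplified monitoring. The rule is therefore uneven in a comparison that these outcomes are meant to serve.

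3. The randomisation stratum appears in no model, although Table 2 shows that the monitoring options differ by site. This is the weakest of the three.

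**Working it through.** **Time point.** Week 144 is 144/52 × 12 ≈ 33 months. Even the post-study period has no 48-month visit.

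**Reproducing the plan's cost power.** Section 11.2 gives a mean of CHF 25,000, an SD of CHF 8,000, 92 per group and two-sided 5%. A 10% difference is CHF 2,500. The standard error is 8,000 × √(2/92) ≈ 1,180. The noncentral t distribution gives 56% power, against about 55% stated. The figure reproduces.

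**Cost of omitting baseline.** Each factor compares 92 with 92. Work in units of the week-48 SD, with equal SD at baseline and week 48. The correlation ρ is not in the protocol; 0.5 to 0.8 is assumed.

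- Standard error of the week-48 comparison: √(2/92) = 0.147.
- Difference detectable with 80% power: (1.96 + 0.84) × 0.147 = 0.413 SD.
- With baseline as a covariate, the variance is multiplied by 1 − ρ² and the detectable difference by √(1 − ρ²).
- For the change score, the variance is multiplied by 2(1 − ρ).
- The typical (one standard error) chance baseline difference carried into the unadjusted estimate is ρ × 0.147.

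| Assumed ρ | Variance inflation 1/(1 − ρ²) | Detectable, week-48 mean | Detectable, change score | Detectable, baseline-adjusted | Carried imbalance |
|---|---|---|---|---|---|
| 0.5 | 1.33 | 0.413 SD | 0.413 SD | 0.358 SD | 0.07 SD |
| 0.7 | 1.96 | 0.413 SD | 0.320 SD | 0.295 SD | 0.10 SD |
| 0.8 | 2.78 | 0.413 SD | 0.261 SD | 0.248 SD | 0.12 SD |

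To match the adjusted analysis, the planned one would need about 92/(1 − ρ²) = 123, 180 or 256 patients per group. A true difference of 0.3 SD has 53% power as planned and 65%, 81% or 92% with baseline. Adjustment also does at least as well as the change score at every ρ shown.

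**Which outcomes have a week-36 value.**

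| Outcome | Standard monitoring | Patient-centered |
|---|---|---|
| CD4 count, lipids (and so Framingham risk) | yes | no |
| Glucose, creatinine (GFR) | yes | only with DTG plus metformin |
| HIV-DNA | no | no |
| Weight (examination at day 0, weeks 24 and 48) | no | no |
| Quality of life | both arms in 9.3.5; neither arm in 9.1 and 9.2.2 | same |

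The rule is uneven for the first row, and for the second outside the metformin subgroup. For the others the two arms are alike.

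**Size of the asymmetry, as an illustration.** Assume that 10% miss week 48 and that half of those attended week 36. Standard monitoring then analyses 92 × 0.90 + 92 × 0.10 × 0.5 = 82.8 + 4.6 = 87.4 patients, of whom 4.6 are carried forward. The patient-centered arm analyses 82.8, none carried forward.

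**Centre.** If centre explains 5%, 10% or 15% of the cost variance (assumed), the residual SD is 8,000 × √(1 − R²), and power for the 10% difference goes from 56% to 58%, 60% or 63%. For the binary primary outcome, simulated power was 82% with or without centre as a stratum.

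**The case against.** Much can be said for the plan. Under randomisation, a difference in week-48 means estimates the same effect as a difference in changes, so the estimand is not lost. The month wording is plainly a slip. Section 11.4.3 also considers a linear mixed model on all measurements with a treatment-by-time term. If baseline is among those measurements, that model uses it. Section 11.5 says only that carry-forward will be considered for secondary outcomes, and it plans sensitivity analyses. Section 11.4.6 leaves detail to a statistical analysis plan.

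This limits the point but does not remove it. The mixed model is supportive and the role of baseline in it is unstated, while the main model's adjustment set is spelled out and excludes baseline. The exclusion rule for continuous outcomes makes sense only if week-36 values stand in for week 48.

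Several stronger readings are tempting and are not supported:

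- **Bias or inflated type I error from omitting baseline.** Neither follows; the cost is precision and uncorrected chance imbalance.
- **Section 11.2's power statement is refuted.** It says "We will also have substantial power to detect small-to-moderate differences in many of the secondary outcomes" and gives no effect size. Without baseline, power is 27% at 0.2 SD and 53% at 0.3 SD, but 77% at 0.4 SD and 92% at 0.5 SD.
- **The carry-forward rule distorts the drug comparison.** The 1:1:1:1 factorial balances monitoring type across DTG + FTC and cART.
- **The primary Mantel-Haenszel estimate needs centre strata.** Seven centres by two monitoring types makes 14 strata. The two sites planned at 12 patients would have 12/2 = 6 per stratum, 3 per treatment arm. At 97% and 94% success, about 8 of the 14 strata would be expected to have no failure. The gain is near zero.

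**Conclusion.** The point holds for secondary and safety outcomes. The stated main analysis gives up precision that the collected data could supply: a variance 1.33 to 2.78 times larger than necessary for ρ between 0.5 and 0.8. That range is an assumption; the lower the true correlation, the smaller the loss. It also names a time point that the trial does not have.

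The carry-forward rule, if applied to secondary outcomes, treats a missing week-48 value differently in the two monitoring arms for CD4 count, lipids and Framingham risk, and for glucose and GFR outside patients on DTG plus metformin. The number affected depends on dropout, and the 4.6 patients above are illustrative.

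Adding centre is a modest improvement, worth making in the linear models because it is the randomisation stratum. Nothing here touches the validity of the non-inferiority conclusion. The changes should be made, but the trial does not stand or fall on them.

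**What to change.** 1. **Section 11.4.2, time point:** replace 48 months with week 48.
2. **Section 11.4.2, model:** analyse each continuous outcome that has a baseline measurement by linear regression of the week-48 value on treatment, monitoring, baseline value and centre. State that for CD4 count and chemistry the baseline is the screening value, since the flow chart schedules none at day 0. Treatment satisfaction is assessed only at week 48 in section 5.2, so it takes the same model without a baseline term.
3. **Section 11.4.2, costs:** add centre to the cost regression.
4. **Section 11.5:** drop week-36 carry-forward for the laboratory outcomes and use one rule for both monitoring arms, namely baseline plus week-48 data under missing-at-random.
5. **Sections 9.1, 9.2.2 and 9.3.5:** reconcile whether quality of life is collected at week 36.

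Leave the Mantel-Haenszel stratification of the primary outcome unchanged.

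The cost is wording in the protocol or the statistical analysis plan and a few degrees of freedom: one for baseline and six for seven centres. No extra data or patients are needed.

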| Statistical Considerations: | 
DTG + FTC dual therapy is expected to be non- inferior to standard-of-care using a 12% non-inferiority margin assuming that 92% of patients are virologically suppressed at week 48 in the two comparison arms.
 
We will evaluate the proportion of patients with viral suppression at week 48 in each arm, and compute a Mantel-Haenszel risk difference (DTG+FTC minus cART) stratified by monitoring type with a two-sided 95% confidence interval. If the lower confidence limit is higher than -12% we will conclude non-inferiority. If the lower confidence limit is below -12% we will conclude that DTG + FTC is potentially inferior to cART. Per protocol (PP) and intention-to-treat (ITT) analyses will be performed. Exclusion criteria for PP will be: patients who discontinue treatment prematurely for reasons other than death, patients with a treatment adherence of less than 80%, or those who do not have HIV-1 RNA results available at week 48. For ITT analysis, all randomized patients will be analysed in the allocated group regardless of any protocol violations.
 |
| GCP Statement:              | 
This study will be conducted in compliance with the protocol, the current version of the Declaration of Helsinki, the ICH-GCP or ISO EN 14155 (as far as applicable) as well as all national legal and regulatory requirements.
                                                                                                                                                                                                                                                                                                                                                                                                                                                                                                                                                                                                                                                                                                                                                                                                                                                                          |

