DTG is well tolerated with only 2% to 3% of patients discontinuing the drug for adverse events in phase III trials. Frequent side-effects include sleep disturbance, gastro-intestinal complaints, headache, and respiratory tract complaints; most were grades 1 or 2 in clinical trials (13, 14). No life threatening adverse events were observed. Rates of psychiatric adverse events, i.e. insomnia, anxiety, depression or suicidality, were low in treatment-naïve phase III/IIb trials of DTG with frequency of withdrawal as low as 5% (51). However, observational studies have reported higher rates of central nervous system side effects (up to 20%) in treatment-naïve or -experienced patients receiving DTG (52, 53) with discontinuation rates due to central nervous system adverse events from 0.6% to 3.4% (52, 54-56). A retrospective cohort study in the Netherlands reported up to 13.7% of discontinuation rate due to adverse event on DTG (57) and another in Germany found that women and older patients were more at risk of discontinuing DTG for neuropsychiatric side effects (58). DTG is also lipid neutral with fewer elevations of low-density lipoprotein of grade 2 or higher compared to efavirenz or boosted darunavir in the SINGLE and FLAMINGO trials (12, 59). However, there are no data on the effect of DTG on body fat composition and the associated cardiovascular risk or bone mass density, which are growing concerns in our aging HIV population.

Drug interactions are very few (43), another advantage of the compound. DTG is a substrate of UGT1A1, CYP3A4, UGT1A3, and UGT1A9. Only 1% of potential drug-drug interactions are considered to be at risk (Figure 2). DTG should be used at the dose of 50mg twice daily with rifampicin, a potent inducer of UGT1A1 and CYP3A4. Co-administration with other inducers of UGT1A1 and CYP3A4 such as carbamazepin, oxcarbamazepin, phenytoin, phenobarbital and St. John's wort should be avoided. As DTG inhibits the renal transporter OCT2, it is contraindicated with the antiarrhythmic dofetilide (which is not authorized in Switzerland) and caution is needed when co-administered with metformin. DTG should be taken with food when administered with calcium or iron supplementation or vitamins intake as well as with magnesium or aluminium-containing antacids (14).

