## **7.4 Criteria for withdrawal / discontinuation of participants**

Participants will be withdrawn from the trial if:

1. The subject withdraws consent; in this case the patient will continue the antiretroviral treatment with a standard-of-care treatment (cART) and will continue regular follow-up with his/her treating physician;
2. Clinical reasons believed to be life-threatening by the physician, even if not addressed in the toxicity management protocol;
3. Subject is judged by the investigator to be at significant risk of failing to comply with the provisions of the protocol so as to cause harm to self or seriously interfere with the validity of the study result.
4. Study routine procedure must be stopped due to safety concerns.

Withdrawn participants will not be replaced.

Participants in the DTG + FTC dual therapy maintenance arm will discontinue study drugs if (non exhaustive list):

- diagnosed with virological failure defined as plasma HIV-RNA  $\geq 100$  copies/ml on two consecutive occasions;
- become pregnant
- start breastfeeding;
- requiring to use prohibited concomitant medications such as carbamazepine, oxcarbamazepine, phenytoin, phenobarbital, rifampicin or St John's Wort;
- presenting serious adverse events that necessitate to stop dolutegravir and/or emtricitabine;
- reasons related to conceiving and DTG potentially safety issue.

They will still be included in the study, continue their antiretroviral treatment with a standard cART. They can be switched to their previous ARV regimen or to a different one according to the genotypic resistance testing, drug-drug interactions profile and/or clinical evolution, and will complete study procedures until week 48. If the new regimen still fulfills the eligibility criteria the subject can continue the study, otherwise the subject will be withdrawn from the trial. In case of a pregnancy the viral load measurement will be performed once per month accordingly to the EACS guidelines.

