## **11.4 Planned Analyses**

### **11.4.1 Datasets to be Analysed, Analysis Populations**

As recommended by the CONSORT statement (106), two analysis sets will be performed: per-protocol (PP) and intention-to-treat (ITT).

For PP analysis, we will exclude patients for the following reasons: patients who discontinue treatment prematurely (< 47 weeks), unless virological failure occurred before, patients with a treatment adherence of less than 80% while on treatment, those who do not have HIV-1 RNA results at week 48 (+/-21 days), unless virological failure occurred before, or patients with major protocol deviation(s) (i.e. any failure to obtain informed consent, violation of any inclusion criteria, not receiving the allocated treatment or monitoring). Per-protocol and intention-to-treat analyses should reach the same conclusion to consider DTG + FTC as non-inferior to standard treatment.

For ITT analysis, all randomized patients will be analysed in the allocated group regardless of any protocol violations.

All drop outs will be described and reasons for their discontinuation will be given where possible.

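### The per-protocol comparison of adverse events leaves out patients whose adverse event ended treatment, so it gives a biased second safety result beside the complete ITT one

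*Protocol*

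**What the plan says.** Section 11.4.2 of the protocol lists the secondary categorical outcomes for the Mantel-Haenszel comparison between arms. They include the proportions "of loss of future treatment options, of adverse events, of serious adverse events, of CSN adverse events, of CNS symptoms". The section ends with: "All analyses will be performed in the PP dataset and in the ITT dataset".

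Section 11.4.1 defines two sets. For ITT, "all randomized patients will be analysed in the allocated group regardless of any protocol violations". The PP set excludes "patients who discontinue treatment prematurely (< 47 weeks), unless virological failure occurred before". It also excludes patients with no week 48 HIV-RNA result (again unless virological failure came first), with low adherence, or with a major protocol deviation.

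The synopsis words the first PP exclusion differently: "patients who discontinue treatment prematurely for reasons other than death". Neither version exempts a stop due to an adverse event.

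Section 7.4 gives, among the reasons for stopping study drugs in the DTG + FTC arm, "presenting serious adverse events that necessitate to stop dolutegravir and/or emtricitabine". Section 11.4.5 (safety analysis) names no analysis set.

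**The concern.** An adverse event that makes a patient stop before week 47, without earlier virological failure, takes that patient out of the PP set. The event then cannot appear in the PP comparison of adverse events. Inclusion depends on the outcome being compared, and the events removed are those that say most about tolerability.

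The direction is probably not neutral. Patients in the DTG + FTC arm are switched to a study regimen, while controls stay on a regimen that they already tolerate. Stops for adverse events should therefore fall mainly on DTG + FTC, and the PP result would make that arm look safer. The report could then carry two safety results that differ, and the protocol gives no rule on which one governs safety.

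**Working it through.** The plan attaches no figure to this point, so there is none to reproduce. The check is a reading of the set definitions, followed by arithmetic on scale.

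**Which patients are lost.**
- Adverse event, treatment continues: in ITT and, if otherwise eligible, in PP.
- Adverse event, stop before week 47, no earlier virological failure: in ITT, not in PP.
- Adverse event, stop at or after week 47 or after virological failure: in ITT, and not removed from PP by this clause.
- Death before the week 48 window, no earlier virological failure: in ITT, not in PP. The synopsis exempts death from its discontinuation clause, but its clause on missing week 48 HIV-RNA removes the patient anyway.

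The data exist. Under section 7.4, patients who stop DTG + FTC stay in the study and complete procedures to week 48, unless the new regimen no longer meets the eligibility criteria.

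**How many patients.** Section 3.2 gives 2% to 3% stopping DTG for adverse events in phase III trials, and one retrospective cohort "reported up to 13.7% of discontinuation rate due to adverse event on DTG". With 92 patients per group (synopsis):
- 0.02 × 92 = 1.8 and 0.03 × 92 = 2.8, so about 2 to 3 patients;
- 0.137 × 92 = 12.6, so about 13 patients.

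**Effect on the risk difference.** Let b be the percentage of each arm with an event but no stop, d the percentage of DTG + FTC patients who stop for an event, and 1 the corresponding percentage on cART. The values of b, the 1% and the intermediate d = 5 are assumptions; the protocol gives none of them.
- ITT difference = (b + d) − (b + 1) = d − 1 points.
- PP difference = 100 × [b/(100 − d) − b/99] points.
- Share lost = 1 − PP/ITT = 1 − 100b/[99(100 − d)].

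| b (assumed) | d | ITT difference | PP difference | Share lost |
|---|---|---|---|---|
| 14 | 2 | 1.0 | 0.14 | 86% |
| 14 | 5 | 4.0 | 0.60 | 85% |
| 14 | 13.7 | 12.7 | 2.08 | 84% |
| 50 | 2 | 1.0 | 0.52 | 48% |
| 50 | 5 | 4.0 | 2.13 | 47% |
| 50 | 13.7 | 12.7 | 7.43 | 41% |

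Two other sets of assumptions show how far the share can move.
- **No cART stops, and the same event proportion (10% or 20%) among all patients who do not stop.** The ITT difference is d × (1 − proportion): 1.6 to 2.7 points for d of 2% to 3%, and 11.0 to 12.3 points for 13.7%. The PP difference is 0 throughout, so the whole excess is lost.
- **Most events do not end treatment.** Section 3.2 reports CNS side effects on DTG in up to 20% of patients, but stops for CNS events in only 0.6% to 3.4%. Taking 20% and 3.4% together, the DTG + FTC proportion is 20% in ITT and (20 − 3.4)/(100 − 3.4) = 16.6/96.6 = 17.2% in PP. The loss is then modest.

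**The case against.** The strongest reply is that the sentence at issue also requires the ITT analysis, which keeps every randomised patient and so every event. Section 11.4.1 has drop-outs described with reasons where possible. Under section 11.3, serious and grade 3/4 adverse events go to the DSMB every six months with no PP restriction. A reader might infer that treatment-ending events vanish from the trial's safety assessment. The documents do not support that.

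A reader might also infer that PP and ITT carry equal weight for safety, because section 11.4.1 requires both to agree. That rule concerns the non-inferiority conclusion only, and no safety decision in the protocol rests on the PP set. Section 11.4.5 does not say that it uses PP, so the point is firm for the comparisons in 11.4.2 and reaches 11.4.5 only by extension. The statistical analysis plan may define a safety set, and the lack of one in the protocol is not the complaint.

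Two further inferences go too far. One is that only the DTG + FTC arm starts new drugs. INSTI-based regimens are eligible, the protocol distinguishes patients new to DTG, and section 8.1.2 accepts within-class switches in the cART arm. The other is that most of the excess always disappears; the working shows that this depends on assumed rates. The 13.7% is an upper figure from one cohort.

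All of this limits the size of the point. It does not remove it: the plan prescribes the PP safety comparison, and that comparison is selected on its outcome.

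**Conclusion.** The point holds in a limited form. As written, section 11.4.2 calls for a PP comparison of adverse events, SAEs, CNS adverse events and CNS symptoms from which events that end treatment before week 47 are removed, unless virological failure came first. The defect is a biased second safety result beside a complete one. It is not a loss of events from the trial, and it does not touch the non-inferiority analysis.

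About 2 to 3 DTG + FTC patients would be removed at the phase III rates, and about 13 at the cohort's upper figure. Those counts rest on past DTG rates applying to this arm. That the bias favours DTG + FTC is probable, because that arm is the one switched, but it is not certain. No single figure for the share of an excess that is hidden can be drawn from the protocol. It is about 84% to 86% with a 14% background and 41% to 48% with a 50% background, both with 1% of cART patients stopping, and other assumptions widen the range. Section 11.2 already concedes low power for rare outcomes such as adverse events, so the removal of even two or three patients is worth avoiding.

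**What to change.** Replace the closing sentence of section 11.4.2 with wording such as: *Efficacy analyses will be performed in the PP and ITT datasets; adverse event, SAE, CNS adverse event and CNS symptom outcomes will be analysed in all randomised patients as allocated.* Name the same set in section 11.4.5. Laboratory safety outcomes should use all randomised patients with data, subject to the rule in section 11.5 that leaves patients with no week 36 or week 48 value out of continuous analyses. The synopsis and section 11.4.1 should also be brought into line on how the PP set treats death.

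The cost is a sentence in each of two sections, plus the alignment of the PP definition. The change means fewer analyses and affects neither the sample size nor the data collected.
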